## Abstract

**Background:**

Chronic obstructive pulmonary disease (COPD) is a progressive, debilitating disease associated with significant clinical burden and is estimated to affect 15 million individuals in the US. Although a large number of individuals are diagnosed with COPD, many individuals still remain undiagnosed due to the slow progression of the disorder and lack of recognition of early symptoms. Not only is there under-diagnosis but there is also evidence of sub-optimal evidence-based treatment of those who have COPD. Despite the development of international COPD guidelines, many primary care physicians who care for the majority of patients with COPD are not translating this evidence into effective clinical practice.

**Method/Design:**

This paper describes the design and rationale for a randomized, cluster design trial (RCT) aimed at translating the COPD evidence-based guidelines into clinical care in primary care practices. During Phase 1, a needs assessment evaluated barriers and facilitators to implementation of COPD guidelines into clinical practice through focus groups of primary care patients and providers. Using formative evaluation and feedback from focus groups, three tools were developed. These include a computerized patient activation tool (an interactive iPad with wireless data transfer to the spirometer); a web-based COPD guideline tool to be used by primary care providers as a decision support tool; and a COPD patient education toolkit to be used by the practice team. During phase II, an RCT will be performed with one year of intervention within 30 primary care practices. The effectiveness of the materials developed in Phase I are being tested in Phase II regarding physician performance of COPD guideline implementation and the improvement in the clinically relevant outcomes (appropriate diagnosis and management of COPD) compared to usual care. We will also examine the use of a patient activation tool - *‘MyLungAge*’ - to prompt patients at risk for or who have COPD to request spirometry confirmation and to request support for smoking cessation if a smoker.

**Discussion:**

Using a multi-modal intervention of patient activation and a technology-supported health care provider team, we are testing the effectiveness of this intervention in activating patients and improving physician performance around COPD guideline implementation.

**Trial registration:**

ClinicalTrials.gov, NCT01237561

## Background

Chronic Obstructive Pulmonary Disease (COPD) is a serious public health problem and is estimated to affect 15 million individuals in the United States [1]. Although the prevalence of COPD is increasing, the true burden of the condition is underestimated because COPD runs an insidious course and often results in an undiagnosed initial phase [2]. Consequently COPD is usually not recognized until it is “clinically apparent and moderately advanced” [3] and, in fact, COPD is most often diagnosed in the fifth or sixth decade even though the disease may actually start much earlier in life [4,5].

A joint activity between the National Heart, Lung and Blood Institute and the World Health Organization helped to develop and publish the Global Strategy for the Diagnosis, Management, and Prevention of Chronic Obstructive Lung Disease (GOLD) aimed at increasing awareness of COPD among health care providers and the general public and to provide comprehensive treatment guidelines with the goal of decreasing COPD related morbidity and mortality [6,7]. Despite the development of GOLD guidelines which provide guidance for appropriate prevention and management strategies, substantial gaps exist between the development of the guidelines and their implementation and dissemination in clinical practice. Consequently, COPD, which is a systemic disease with symptoms that overlap with other respiratory illnesses, remains underdiagnosed and undertreated [8-10].

The GOLD COPD guidelines have been developed to emphasize the importance of performing spirometry to make a firm diagnosis of COPD as well as to help stage COPD severity and guide specific treatment steps [11]. The guidelines recommend performing spirometry on all individuals with a history of repeated exposure to environmental pollutants and/or cigarette smoke exposure, a family history of COPD, or the presence of a chronic cough, sputum production, or shortness of breath. It has been suggested that “spirometry can be incorporated into family medicine practice with acceptable levels of technical adequacy and accurate interpretations” [12] based on the fact that improvements in spirometry equipment provide immediate feedback related to technical adequacy. We were interested in examining whether spirometry testing could be incorporated into primary care practice and potentially impact both the diagnosis and subsequent management of COPD. For the proposed study, we have provided office spirometers with adequate technical training to both intervention and usual care practices.

Current data suggest that there is underutilization of spirometry for detection and diagnosis of COPD [13]. Various reasons given by primary care physicians for not utilizing spirometry include: limited access to spirometry, uncertainty about the impact of the test, inadequate or lack of reproducibility of patient effort, lack of provider training, difficulty in interpreting results, reimbursement issues, and time constraints in busy practice settings [13,14]. Despite dissemination of the newer recommendations in an effort to increase primary care physician’s utilization of COPD guidelines, many primary care physicians remain unaware of COPD guidelines and the diagnosis of COPD continues to be based on clinical findings alone [15]. In summary, it appears that many patients with COPD are not diagnosed or staged with spirometry and therefore undertreated. Given this treatment gap, primary care providers will be the focus of the enhanced COPD guideline implementation and will allow us to examine whether a multi-modal intervention tailored to primary care practices will improve the care of patients with COPD.

## Methods/Design

This 5 year, National Institutes of Health (NIH) funded study is evaluating the translation of the Gold COPD guidelines into primary care practice. This study is based upon the premise that an informed, activated patient will interact with a prepared, proactive team to improve COPD diagnosis and management [16-20]. During Phase I, a needs assessment evaluated barriers and facilitators to implementation of COPD guidelines into clinical practice through focus groups of primary care patients and providers. Using formative evaluation and feedback from the focus groups, three tools were developed, refined and pilot tested. These include: 1) a patient activation tool on an iPad platform, 2) a Lung Age decision support tool to be used by primary care providers, and 3) a COPD patient education toolkit. During Phase I, procedure manuals, study protocols, and data collection instruments were also developed and pilot tested. During Phase II, a block, randomized design cluster trial (RCT) is currently underway with 30 primary care practices throughout the state of Rhode Island and southeastern Massachusetts. The effectiveness of the materials developed in Phase I is being tested in Phase II regarding physician performance of COPD guideline implementation and the improvement in the clinically relevant outcomes (appropriate diagnosis and management of COPD) compared to usual care. We are also examining the use of the patient activation tool (iPad) - *‘MyLungAge*’ to prompt patients to talk with their health care provider regarding their lung health and risk for COPD (Figure 1).

**Figure 1 F1:**
[figure not shown]
Overview of the RCT study design in phase II of translating the COPD guidelines into primary care practice.

For the RCT of primary care practices, the unit of randomization is the practice. Practice, provider, and patient level outcomes are being assessed that include: pre- and post-assessment of practice characteristics, provider characteristics, and patient information based on chart audits. Patient chart audits are based on two samples: 1) one is based on an identified sample of at-risk or COPD patients (to examine management of these patients) and 2) the other is based on a de-identified random audit of charts from all practices. The first audit based on an identified sample of at-risk or COPD patients, who gave Informed Consent, are being conducted in the pre- and post-intervention periods. A random chart audit of de-identified patient outcomes both pre- and post-intervention is being conducted to determine the degree of selection bias inherent in the informed consent process. In addition, semi-quantitative assessments of the reach of the intervention are being undertaken on a regular basis through counting the number of ‘hits’ on the *MyLungAge* (iPad) patient activation tool located in each of the intervention practices and the number of tests initiated on the spirometer for each of the intervention providers. To better understand the workflow issues, strengths and weaknesses of our implementation strategy, a qualitative study of physicians’ understanding and adherence to the COPD guidelines, and a qualitative study of patients’ attitudes and perceptions regarding acceptance of COPD management recommendations and COPD medication adherence are being undertaken one year post intervention. This study is approved by the Memorial Hospital of RI Institutional Review Board.

### Providers

We are performing a two-group RCT, testing the effectiveness of translating the COPD guidelines into clinical practice, with primary care physicians’ practices as the unit of randomization and evaluation. The intervention arm receives an intervention of academic detailing, an iPad-based patient activation tool that will be placed in the examination rooms, a netbook running a COPD guideline decision support tool, a COPD patient education toolkit including a website, and a portable spirometer and a printer. The usual care arm receives visits on the same schedule as the academic detailing visits, a website link to the GOLD Guidelines, a printer, and a portable spirometer. The intervention is of one-year duration. We are evaluating the use of the interactive tool and use of the patient activation tool through tracking software.

### Patients

A cover letter was sent to a random selection of eligible patients (patients 40 years or older who had been seen at least once in the past 2 years (active patients) by their primary care provider). The patients received information regarding the study, were informed that their provider was participating in the study, and that they would receive a telephone call by one of the research study staff to invite them to participate in the study, to ask them to grant permission for auditing of their medical record at baseline and one-year post intervention, and to obtain Informed Consent. During the telephone call, patients received additional information regarding the study, were asked to provide audio consent and completed a 15-minute telephone interview that included demographic and medical history data and information regarding the patient’s knowledge, skills and behaviors necessary to create an activated patient for managing their own health care (PAM-a patient activation measure) [21].

### Measures

Data collection for practices includes: type of practice (HMO, single specialty, etc.); degree of managed care; service options (dietitian, nurse counseling, etc.,); numbers of personnel (physicians, RN, LPN, Nurse Practitioners, medical assistants, physician assistants, clerical, other); use of non-physician personnel, use of ancillary services in office (office laboratory, phlebotomy, dietitian, consultants); ancillary services in the building; who returns phone calls (physician vs. other); record systems (computerized, written, dictated); physical environment (rural, urban, suburban), socioeconomic class of patients seen; office organization (evening hours, weekend hours); and volume of visits (number scheduled, number of unscheduled, total number of patients, number of patient care hours, number no shows). Data collection of providers includes: 1) demographic information (age, gender), years in practice, type of provider (physician, nurse practitioner, physician assistant), specialty (general practitioner, family physician, obstetrics/gynecology, medicine/pediatrics, general internist, other); 2) practice characteristics (number of office visits, nursing home visits, and home visits seen in a typical week); 3) self-report of preventive screening (cholesterol screening, glucose screening for diabetes, self-report of counseling for smoking cessation, diet, physical activity) and 4) self-reported familiarity with COPD guidelines and feelings about COPD guidelines. Patient information from medical records includes: 1) socio-demographic factors- age, gender, race/ethnicity, insurance status, pharmacy benefits, marital status, number of visits in past year; 2) COPD risk factors (tobacco smoke, occupational dusts and chemicals, smoke from home cooking and heating fuel); 3) co-morbid conditions (i.e., coronary heart disease, congestive heart failure, arrhythmias, hypertension, stroke, liver disease, renal disease, arthritis, diabetes, malignancies, Parkinson’s disease, depression, osteoporosis); 4) functional status; 5) cachexia; 6) medications; 7) vital signs-height, weight, waist circumference, body mass index; 8) laboratory- hemoglobin, hematocrit; 9) provider documentation of weight loss, dietary assessment, dietary treatment or referral, physical activity assessment, and treatment for smoking cessation advice/ counseling/referral; 10) indicators needed to perform spirometry: dyspnea (worse with exercise, persistent, increased effort to breathe), chronic cough, chronic sputum 11) provider documentation of the need for pharmacotherapy; 12) provider documentation of adverse effects of COPD medications; and 13) intervention specific outcomes- documentation of *MyLungAge* in the chart, using printed SOAP notes or patient education page notes, use of the study smoking cessation material, and documentation of referral to the *MyLungAge* website. Data collection by chart audit is performed at baseline and again one-year post intervention. In addition, charts are audited for family history of COPD, smoking status, chest x-rays, ECGs, α_1_-antitrypsin deficiency screening, COPD symptoms (prolonged or progressive cough, sputum production, persistent or progressive dyspnea), exposure to lung irritants, exposure to secondhand smoke, documentation of spiromety, documentation of pulmonary disease, COPD, cystic fibrosis, interstitial lung disease, sarcoidosis, tuberculosis, pulmonary hypertension, thoracic surgery, immunizations and vaccines. Adherence to the COPD guidelines is based on an adherence tool developed by a consensus panel of 6 individuals with expertise in COPD and will include information on documentation of: exposure to tobacco smoke and occupational dust and chemicals; smoking status; appropriate treatment, increase in symptoms, influenza and pneumococcal vaccine; need for oxygen therapy; and assessment of history of CVD or CVD risk factors.

### Sample size considerations

The primary aim of this RCT is to determine and compare the proportion of participants who are appropriately diagnosed with COPD between the intervention and usual care arm. The clusters (i.e. practices) are randomly assigned to the intervention or usual care arm. Taking the intra-cluster correlation into account in the planning phase of the study is critical since failure to do so may result in an underpowered study. The intra-cluster correlation (r) is estimated to be between 0.01-0.02 based on previous findings [22]. For this study, we enrolled 30 practices, 15 for each group. Using a two-side type I error of 5%, the projected number of random charts per practice needed for a power of 80% is 35 for r=0.01 and 52 for r=0.02. Similarly, we assume the estimated percentage of patients who were diagnosed with COPD varied from 6% for the control group and 12% for the intervention group. The selection of 100 charts per practice in the random retrospective chart audits gives us reasonable power for all projected COPD outcomes. A total of 3000 charts for the study provide greater power for multivariate analyses, detecting interaction effects, robustness to violations of model assumptions. Given that we have audited 3,604 baseline charts, we have increased efficiency to detect weaker relationships between variables.

### Statistical analyses

Initially, descriptive statistics such as frequency tables for each categorical variable, and minimum, maximum, range, median, mean and standard deviation for each continuous variable will be used to summarize the data as well as detect outliers, data entry mistakes, and missing values. Classical longitudinal plots will be used to identify trends over time in both practice and individual levels. Chi-squared tests, t-tests or non-parametric tests will be used to assess the effectiveness of the randomization procedures by comparing intervention and control groups on baseline variables. Data analyses will be performed using SAS 9.1.3 (SAS Institute, Inc, Cary, North Carolina).

Following intention-to-treat principles, all participants who have been randomized to the two conditions will be included in the analyses. We hypothesize that a greater proportion of patients in the intervention arm will be appropriately diagnosed with COPD after one year compared to the usual care arm. We will use both generalized linear models using GEE (generalized estimating equations) approach and generalized linear mixed models to evaluate the independent effect of intervention after adjusting for patient and provider level covariates, important demographic and confounding factors. To compare COPD guideline adherence to the treatment algorithm recommended for primary care physicians after a one-year intervention in the usual care arm compared to the intervention arm, we will examine the dichotomous variable of whether or not a provider will adhere to the COPD treatment algorithm after a one-year intervention.

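### The planned baseline tests make no allowance for clustering, so patient-level variables can show false imbalance well above the nominal 5%

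*Protocol article*

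**What the plan says.** The protocol article states in Methods/Design that "the unit of randomization is the practice", and under Sample size considerations that "we enrolled 30 practices, 15 for each group". That section also says "Taking the intra-cluster correlation into account in the planning phase of the study is critical" and gives a value: "The intra-cluster correlation (r) is estimated to be between 0.01-0.02 based on previous findings".

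Under Statistical analyses, the baseline comparison is described differently: "Chi-squared tests, t-tests or non-parametric tests will be used to assess the effectiveness of the randomization procedures". The arms are to be compared on baseline variables, with no level of analysis and no cluster adjustment named. The next paragraph names GEE and generalised linear mixed models for the intervention effect, so methods suited to clustered data are specified for the outcome only.

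The Measures section lists baseline data at three levels: practice, provider and patient. The patient list is long and comes from charts: demographics, insurance, risk factors, comorbid conditions, medications, symptoms and vaccinations. The sample size section reports 3,604 baseline charts already audited.

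**The concern.** Ordinary chi-squared, t- and rank tests assume independent observations. Charts from one practice share a catchment, a record system and clinicians, and the whole practice goes to one arm. The variance of the difference between arms is then larger than these tests suppose, and their p-values for patient-level variables are too small.

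The stated purpose makes this matter. The tests are meant to show whether randomisation worked. If it was done properly, any rejection is a chance finding, and ignoring clustering multiplies such findings. A reader of the baseline table could conclude that a sound randomisation had failed. A second harm is possible but conditional: if flagged variables were then used to pick adjustment covariates, the adjustment would be data-driven.

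**Working it through.** **Inputs from the protocol article**
- 30 practices, 15 per arm; ICC r = 0.01 to 0.02; two-sided 5% error; 80% power (Sample size considerations).
- Assumed proportions: "varied from 6% for the control group and 12% for the intervention group" (same section).
- 3,604 baseline charts, so m = 3,604/30 = 120.1 per practice on average. The same section plans 100 per practice; the Outcomes section gives 125.

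**Step 1. Reproduce the plan's own figure.** The article says "the projected number of random charts per practice needed for a power of 80% is 35 for r=0.01 and 52 for r=0.02". For 6% versus 12%, the usual two-proportion formula gives 356 per arm, or 389 with continuity correction. Solving 15m / [1 + (m − 1)r] = n for m gives m = n(1 − r) / (15 − nr). With n = 389:
- r = 0.01: 389 × 0.99 / (15 − 3.89) = 385.11 / 11.11 = 34.7
- r = 0.02: 389 × 0.98 / (15 − 7.78) = 381.22 / 7.22 = 52.8

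These are close to the stated 35 and 52. Without the correction the results round up to 31 and 45. The sponsor's calculation is therefore consistent with the design effect 1 + (m − 1)r.

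**Step 2. Apply the same design effect to an unadjusted baseline test.** With DE = 1 + (m − 1)r, the true rejection rate of a nominal two-sided 5% test is 2[1 − Φ(1.96/√DE)].
- m = 120.1, r = 0.01: DE = 1 + 119.1 × 0.01 = 2.19; 1.96/√2.19 = 1.32; rate 18.5%
- m = 120.1, r = 0.02: DE = 1 + 119.1 × 0.02 = 3.38; 1.96/√3.38 = 1.07; rate 28.7%

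| Charts per practice | r = 0.01 | r = 0.02 |
|---|---|---|
| 100 | 16.5% | 25.6% |
| 120.1 | 18.5% | 28.7% |
| 125 | 19.0% | 29.3% |

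Across the table this is 3.3 to 5.9 times the nominal 5%.

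**Step 3. Check by simulation.** Beta-binomial data were generated for 15 versus 15 practices with no true difference, with 100, 120 or 125 charts per practice and prevalence 9% or 50% (20,000 runs each). At r = 0.01 to 0.02 the unadjusted test rejected in 16% to 30% of runs. A t-test on practice-level proportions rejected in 4.7% to 5.3%.

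**Step 4. Vary the assumed ICC at 120.1 charts per practice.** The article gives no ICC for any baseline variable, so these values are assumptions.

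| Assumed r | True rejection rate |
|---|---|
| 0.001 | 6.4% |
| 0.005 | 12.1% |
| 0.05 | 45.7% |
| 0.10 | 58.5% |

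**Step 5. Other levels.** Practice-level variables have one value per practice, so there is no inflation. For provider-level variables, with an assumed 5 providers per practice and r = 0.01 to 0.02, DE is 1.04 to 1.08 and the rate is 5.5% to 5.9%.

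Equal practice sizes are assumed throughout; unequal sizes would make the inflation slightly larger.

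**The case against.** The strongest reply concerns scope and consequence. The article does not say at which level the baseline tests are run, and it calls practices the unit of both randomisation and evaluation. Practice characteristics are among the baseline variables, and the named tests are valid for them. The ICC was a planning value for sample size and need not describe age, insurance or smoking status. The intervention effect is analysed with methods that handle clustering.

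Most of this stands as a limit, but it does not remove the point. The tests are named for baseline variables without restriction, most of those listed are patient-level chart items, and nothing says they will first be reduced to practice summaries. A separate analysis plan could add such a step, but the method as stated is wrong for these variables.

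Two stronger readings are tempting. A reader might infer that every baseline p-value will be invalid and inflated severalfold; Steps 4 and 5 show that this fails for practice-level variables, barely applies to provider-level ones, and does not hold for patient variables with ICC near zero. A reader might also infer that false baseline signals will reshape the primary model. The article says the models adjust for patient and provider covariates and confounding factors, but nowhere plans to choose them from baseline p-values.

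**Conclusion.** The baseline comparison is wrong as written for patient-level variables, with low impact. At about 120 charts per practice, a nominal 5% test has a true rejection rate of about 18.5% to 28.7%, provided the variable shares the planning ICC of 0.01 to 0.02 and charts are tested individually. The first condition is an assumption and the second is the plain reading of the text. The rate approaches 5% as the ICC nears zero and is higher for more strongly clustered variables.

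The type I error of the GEE or mixed-model comparison is not directly affected. What is at risk is the credibility of the statement on whether randomisation worked. Data-driven adjustment would follow only if flagged variables were used to choose covariates.

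**What to change.** For patient- and provider-level baseline variables, replace the ordinary tests in one of two ways:
- test practice-level summaries (15 versus 15) or use models that allow for clustering; or
- drop the tests and report summaries by arm with standardised differences.

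Either removes the clustering error; the second is the simpler table. Ordinary tests may stay for practice-level variables. Add a sentence that model covariates are fixed in advance and are not chosen from baseline p-values.

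The cost is almost nil: a change of wording and of the baseline table, with no new data and no change to the sample size or the outcome analysis.

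### Two models are named for the one primary hypothesis and none is said to decide; with 30 practices, a GEE without small-sample correction would run at about 7% or more, not 5%

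*Protocol article*

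**What the plan says.** The protocol article, under Statistical analyses, states a single directional hypothesis about appropriate COPD diagnosis at one year. Sample size considerations calls this comparison the primary aim. The analysis sentence that follows the hypothesis reads "We will use both generalized linear models using GEE (generalized estimating equations) approach and generalized linear mixed models", and the effect is to be adjusted for patient- and provider-level covariates and for demographic and confounding factors. The number and identity of these covariates are not given.

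The design is clustered: "the unit of randomization is the practice", and "we enrolled 30 practices, 15 for each group". The sample size rests on a two-sided 5% error, 80% power and a small intra-cluster correlation: "The intra-cluster correlation (r) is estimated to be between 0.01-0.02 based on previous findings".

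The article states no variance estimator, reference distribution, degrees of freedom or small-sample correction for either model. It also does not say that uncorrected errors will be used.

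**The concern.** There are two linked issues.

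**Which model decides.** The text commits to two tests of one hypothesis and ranks neither. For a binary outcome, GEE estimates a population-average odds ratio and the mixed model a practice-specific one, and each has its own standard error. The two can fall on opposite sides of 0.05. Without a rule, the p-value reported as primary could be chosen after both are seen.

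**Whether 5% means 5%.** The ordinary GEE sandwich variance is biased low when clusters are few, and a normal reference ignores the uncertainty in that variance. Both effects push the rejection rate above nominal, and each covariate measured at practice level uses up more of the 30 independent units. If such a test were the one reported, confidence intervals would be too narrow and the type I error would exceed the planned level.

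**Working it through.** **Inputs from Sample size considerations.** 15 practices per arm; two-sided 5% error; 80% power; r = 0.01 to 0.02; diagnosis rates that "varied from 6% for the control group and 12% for the intervention group"; 100 charts per practice.

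**Step 1: the plan's own figure.** The article gives the number of charts per practice "needed for a power of 80% is 35 for r=0.01 and 52 for r=0.02". The two-proportion formula for 6% against 12% with continuity correction gives n = 388.6 per arm. Charts per practice are m = n(1 − r)/(15 − n·r):

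- r = 0.01: 388.6 × 0.99/(15 − 3.886) = 34.6
- r = 0.02: 388.6 × 0.98/(15 − 7.771) = 52.7

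These agree with 35 and 52 within rounding. Without the continuity correction (n = 356) the results are 30.8 and 44.3, which do not match. The stated sample size is therefore reproduced.

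**Step 2: rejection rate of an uncorrected GEE, arm only, equal practices.** The sandwich variance divides by 15 in each arm where an unbiased estimate divides by 14. The reported statistic is then a t variable on 28 df inflated by √(15/14). Comparing it with 1.96 gives

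2·P(t28 > 1.96·√(14/15)) = 2·P(t28 > 1.894) = 6.9%.

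With an unbiased between-practice variance but still 1.96, the rate is 2·P(t28 > 1.96) = 6.0%.

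**Step 3: simulation under no effect.** Beta-binomial practices, 30 practices, logistic GEE. The number of practice-level covariates is an assumption throughout.

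| Setting (equal chart counts) | Uncorrected sandwich, normal reference |
|---|---|
| Arm only, 6% rate, r = 0.01 / 0.02, 100 charts | 6.9% / 7.1% |
| Arm only, 9% rate, r = 0.02, 100 charts | 6.6% |
| 3 covariates, 9% rate, r = 0.02, 100 charts | 9.1% |
| 4 covariates, 6% rate, r = 0.01 / 0.02, 100 charts | 9.9% / 9.8% |
| 5 covariates, 9% rate, r = 0.02, 100 charts | 11.1% |
| 6 covariates, 6% rate, r = 0.02, 125 charts | 12.9% |

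The 6%-rate rows use 5,000 runs (Monte Carlo standard error about 0.4 to 0.5 points) and the 9%-rate rows 6,000. In these settings, Kauermann-Carroll variance with a t reference on 30 minus the number of parameters gave about 5% to 6%. With very uneven chart counts (assumed coefficient of variation 0.6) it gave 6.1% with arm only and 6.7% with four covariates, against 8.9% and 12.5% uncorrected.

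**Step 4: does the choice of model matter?** In a further 2,000 null runs per setting (9% rate, r = 0.02, 100 charts), an uncorrected sandwich z-test was paired with a maximum-likelihood logistic mixed model using t on 30 minus the number of parameters. At least one of the two was significant in 7.2% (arm only), 10.8% (three covariates) and 11.4% (five). Among those trials the models disagreed in 27%, 34% and 31%. The mixed model alone rejected 5.8%, 7.6% and 8.2% with that t reference, and 6.8%, 9.0% and 10.2% with a normal one.

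**Step 5: cost in power at 100 charts per practice.** The design effect is 1 + 99r, that is 1.99 and 2.98. The standard error is √{(0.06 × 0.94 + 0.12 × 0.88) × design effect/1500} = 0.01466 and 0.01794, so 0.06/SE = 4.09 and 3.34. Power with t on 28 df is 97.7% and 89.8%. The usual normal formula gives 98.3% and 91.5%.

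**The case against.** The strongest reply is that this is a condensed journal article. The variance estimator, degrees of freedom and small-sample correction are details it would normally leave to a full protocol or SAP, and neither is shown. That stands: their absence is not in itself an error. A reader might infer from the text that the 5% level is broken as planned, but the document does not support this, because it never commits to an uncorrected sandwich variance or a normal reference.

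The larger error rates also depend on assumptions. The article plans patient- and provider-level adjustment but gives no count, and it does not say that the practice characteristics it collects will enter the model. Provider covariates behave like practice-level ones only where a practice contributes a single provider, and patient-level covariates matter less. Spread in chart counts is likewise assumed. Without these assumptions the inflation is about 2 points.

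A reader might also infer that the two models answer materially different questions. At 6% against 12% they hardly do: the marginal odds ratio is (0.12/0.88)/(0.06/0.94) = 2.14, and the practice-specific one is about 2.15 to 2.17 for r between 0.01 and 0.02. Disagreement would come mainly from the standard errors and reference distributions.

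The sandwich bias does not carry over in full to a mixed model (6.0% in Step 2 with an unbiased variance), although a maximum-likelihood fit still exceeded 5% in Step 4. Finally, Kauermann-Carroll is one acceptable correction among several.

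What remains is the stated use of both models for one hypothesis with no primary. An unseen SAP might rank them, but the text as it stands does not.

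**Conclusion.** The point holds in a limited form. The article fixes two models for one primary hypothesis and does not say which decides, so the headline p-value is not uniquely defined. This rests on the text alone.

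The type I error concern is conditional. If the deciding analysis were a GEE with the ordinary sandwich variance and a normal reference, the rate would be about 7% with arm only, and about 9% to 11% under an assumed three to five practice-level covariates. The first figure follows from 15 practices per arm; the second depends on a covariate count that the document does not give.

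The sample size is not in question: the stated 35 and 52 charts reproduce, and the planned 100 leave ample power under a corrected test. This should be settled before outcome data are analysed, but it does not undermine the design.

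**What to change.** Before the outcome analysis:

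- Name one primary model and the effect it estimates. One option is a logistic GEE clustered on practice, with a small-sample corrected variance (Kauermann-Carroll or equivalent) and a t reference on 30 minus the number of practice-level parameters. A mixed model with a suitable degrees-of-freedom method is equally defensible. Whichever is chosen, state its small-sample method.
- Fix a short list of practice-level covariates in advance.
- Label the other model as a sensitivity analysis that does not decide the hypothesis.

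The cost is a few lines of code and slightly wider intervals. The power loss shown in Step 5 is 0.6 points at r = 0.01 and 1.7 points at r = 0.02, so no further practices or charts are needed. If chart counts prove very uneven, check how well the chosen correction holds its level, since it ran slightly above 5% in that setting.
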